### Cost-effectiveness data collection

To estimate the provider costs of the different dispensing intervals per patient treated, we will create an inventory of all resources used to achieve the observed study outcomes from study enrollment to the 12-month, 24-month, and 36-month time points, including ART medications, non-ART medications, laboratory tests, outpatient clinic visits, other clinic services provided, inpatient care visits, fixed costs of patient care, and depreciated investment costs of establishing capacity for multi-month dispensing (e.g., medication storage capacity, pharmacy infrastructure, staff training, etc.). Data will be abstracted from patients’ medical records and the site’s performance reports (e.g. for patient volumes served) and finance and procurement records (for unit costs). Where necessary, cost data will also be obtained from national sources (e.g. Ministry of Health salary scales), commercial price lists, other cost-related studies underway in the INTERVAL countries, and published sources.

Fixed or indirect costs at the facility level include space, utilities, shared staff such as data clerks or managers, and other resources that do not vary directly with patient numbers, and will be allocated to study patients based on the proportion of total facility resources utilized for ART clinic visits. For example, if 10% of a clinic’s total number of visits per month is for ART patients, then 10% of overall clinic fixed costs will be allocated to ART and divided by the total number of ART patients to estimate a fixed cost for each clinic. If data on monthly clinic visits are not available, fixed costs will be allocated on the basis of space utilization. Data on costs incurred by patients for each of the arms will be collected through the entry visit survey, as described above. We will not estimate costs incurred above the level of individual facilities, such as those incurred by the government for overall HIV program management.

### Data safety and monitoring plan

The first data analysis will be performed when 50% of participants have reached 12 months of follow up. The study will be stopped early if we find a difference (at 12 or 24 months) between 3-month versus 6-month dispensing with a *p* value <0.01. Operational futility may be considered if the observed accrual patterns are exceedingly different than planned, and the protocol team has had a chance to address the shortcomings of accrual.

### Data analysis

#### Primary outcome

Our primary outcome, which is the basis for our sample size estimates and primary analysis, is retention in care at 12 months after study enrollment. Data analyses will begin with descriptive measures about the study population stratified by treatment arm and by facility and presented as medians and interquartile ranges for continuous measures and proportions for categorical variables. These measures will be used to look for large variations by facility and for imbalances between study arms.

We will perform an intention-to-treat analysis for the primary outcome of retention. Our analysis will use a log-linear generalized estimating equation to estimate the risk ratios and associated 95% confidence interval for the effect of each intervention arm compared to standard of care. We will specify facility-level clustering to account for the study design and estimate robust standard errors using an unstructured correlation matrix. Should we identify any baseline imbalances between study arms, we will adjust for these in our multivariable model and report adjusted risk ratios and corresponding 95% confidence intervals.

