## Methods/design

INTERVAL will be a pragmatic, cluster-randomized, non-blinded, non-inferiority trial conducted at 30 health facilities in Malawi and Zambia. It will compare three ART dispensing strategies for stable patients – (1) standard of care, (2) 3-month ART dispensing, and (3) 6-month ART dispensing – on retention in care in Malawi and Zambia.

The study protocol was developed using the SPIRIT (Standard Protocol Items: Recommendations for Interventional Trials) Checklist (see Additional file 1) and adheres to the SPIRIT recommendations. The protocol has been approved by the institutional review board of the University of California, Los Angeles (UCLA), the National Health Sciences Research Council (NHSRC) in Malawi, the Zambia Excellence in Research Ethics and Science (ERES) Converge, the Zambia National Health Research Board (ZNHRB), and the Zambia Medicines Regulatory Authority (ZAMRA). The trial is registered with ClinicalTrials.gov as NCT03101592.

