### Sample size

Our study sample size was estimated for a cluster-randomized non-inferiority trial. With 30 clusters available for randomization, we estimated the sample size assuming a fixed number of clusters (*k*), an equal number of clusters per arm, and an equal number of subjects per cluster. Using a one-sided *Z* test (unpooled) with a significance level of 0.05, we estimated that about 5% of subjects would fail to be retained in care in the standard of care arm and 7.5% to be non-inferior in the 3-month or 6-month study arms. Assuming power of 90% and an intracluster correlation coefficient (ICC) of 0.004 [11], we will need to enroll 271 subjects per cluster for a total of 2710 subjects per arm and 8130 total individuals.

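### Retention is sized as a one-sided 5% non-inferiority test of a 2.5-point difference but analysed as a risk ratio with a 95% interval, which gives about 83–84% power, not 90%, if that interval decides

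*Protocol article*

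**What the plan says.** The Methods/design section fixes the framework: "INTERVAL will be a pragmatic, cluster-randomized, non-blinded, non-inferiority trial conducted at 30 health facilities".

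The Sample size section confirms it ("Our study sample size was estimated for a cluster-randomized non-inferiority trial") and sets the test: "Using a one-sided *Z* test (unpooled) with a significance level of 0.05". The planning rate for the control arm is "about 5% of subjects would fail to be retained in care in the standard of care arm". The tolerated limit for the two intervention arms is given as "7.5% to be non-inferior in the 3-month or 6-month study arms". Power is set at 90% with an ICC of 0.004, and the section arrives at 271 per cluster, 2710 per arm and 8130 in total.

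The Primary outcome section, under Data analysis, says that 12-month retention is the basis of both the sample size and the primary analysis. The analysis is a "log-linear generalized estimating equation to estimate the risk ratios and associated 95% confidence interval", comparing each intervention arm with standard of care. That section gives no margin on the ratio scale, and no rule that sets a confidence limit against a margin.

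**The concern.** The two sections describe the same outcome and the same contrasts with standard of care, but they fix different tests. One is a difference of proportions at one-sided 5%. The other is a ratio reported with a two-sided 95% interval, whose relevant limit corresponds to one-sided 2.5%.

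Two things are at stake. The 90% power was computed for the more lenient level, so it is too high if the reported interval is the one that decides. A result near the margin could also be called non-inferior at one level and not at the other, with nothing in the article to settle which applies. The trial's policy message rests on whether non-inferiority is shown, so the rule should be fixed before outcome data are seen. The first data analysis is planned when half the participants have reached 12 months.

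**Working it through.** **Inputs (Sample size section).** Failure 5% under standard of care; limit 7.5%, so the implied margin is 7.5 − 5 = 2.5 points; one-sided α 0.05; power 90%; ICC 0.004; k = 30/3 = 10 clusters per arm.

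**Reproducing the plan's figure.** With 5% failure in both arms and unpooled variance, the size per arm under individual randomization is

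n = (1.645 + 1.282)² × (2 × 0.05 × 0.95) / 0.025² = 1301.7.

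For a fixed number of clusters,

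m = n(1 − ICC) / (k − n × ICC) = 1301.7 × 0.996 / (10 − 5.207) = 270.5, so 271 per cluster, 2710 per arm and 8130 in total. This matches exactly.

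The alternatives tried do not match. Unpooled variance at 5% v 7.5% gives 444 per cluster, the pooled version gives 446, and one-sided 0.025 gives 441. The stated size is therefore a risk-difference test with a 2.5-point margin at one-sided 5%.

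**Power at the stated size.** Design effect = 1 + 270 × 0.004 = 2.08; effective n = 2710/2.08 = 1303 per arm.

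- *Risk difference.* SE = √(2 × 0.05 × 0.95 / 1303) = 0.00854; 0.025/0.00854 = 2.93. Power is Φ(2.93 − 1.645) = 90.0% at one-sided 5% and Φ(2.93 − 1.960) = 83.3% from a 95% interval.
- *Retention ratio.* Margin 0.925/0.95 = 0.974; −ln(0.925/0.95) = 0.02667; SE of the log ratio = √(2 × 0.05 / (0.95 × 1303)) = 0.00899; quotient 2.97. Power is 90.7% and 84.3%.

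| Scale and margin | 90% interval, Z | 95% interval, Z | 90% interval, t (18 df) | 95% interval, t (18 df) |
|---|---|---|---|---|
| Difference, 2.5 points | 90.0% | 83.3% | 87.9% | 79.1% |
| Retention ratio, 0.974 | 90.7% | 84.3% | 88.6% | 80.1% |

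The t columns are a sensitivity check for 20 clusters per comparison (20 − 2 = 18 df). Holding 90% power (Z) with a 95% interval and 10 clusters per arm would take about 441 per cluster on the difference scale or 410 on the retention-ratio scale.

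**How close the two scales are.** The largest tolerated failure is 5 + 2.5 = 7.5% on both scales at 5% control failure. At 3% it is 5.5% (difference) against 1 − 0.97 × 0.925/0.95 = 5.55% (retention ratio). At 10% it is 12.5% against 1 − 0.90 × 0.925/0.95 = 12.4%.

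**A result on which the level decides.** Suppose observed failure is 5.0% v 5.8%, with effective n 1303 per arm. The SE of the difference is √((0.05 × 0.95 + 0.058 × 0.942)/1303) = 0.00885.

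- Difference: the upper limit is 0.8 + 1.645 × 0.885 = 2.26 points (non-inferior) or 0.8 + 1.960 × 0.885 = 2.54 points (not shown).
- Retention ratio: the lower limit is 0.9764 from the 90% interval (above 0.9737, non-inferior) or 0.9735 from the 95% interval (not shown).

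The verdict changes with the level in the same way on both scales.

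**The case against.** The other side has four fair points.

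- *A limit is stated.* The Sample size section gives 5% and 7.5%, so the tolerated loss can be recovered. A reader might infer that the plan has no margin at all, and the text does not support that. What is missing is the link from that margin to the analysed scale and interval. An article may leave a decision rule to the full protocol or analysis plan. It is still open to criticism where two of its own sections fix different levels for the same outcome, because an added rule could not match both.
- *The scale matters little on the natural reading.* The model is described as an analysis of retention, and virologic suppression, also a favourable event, is to be analysed by identical methods. A retention ratio is therefore the natural reading, and it behaves almost like the difference. A reader might instead take a failure ratio with margin 7.5/5 = 1.5, for which power falls to about 77% (90% interval) or 66% (95% interval) by Z. The text does not favour that reading, so those figures should not carry the point.
- *The 90% is not tied to the difference scale alone.* A reader might infer that it holds only for a risk-difference test. It does not: the retention ratio read against 0.974 with a 90% interval has 90.7% power by Z.
- *The 95% interval may be for reporting only.* The Primary outcome section attaches it to the estimate and does not call it the non-inferiority test. This stands, and it makes the power loss conditional. It does not remove the need to say which interval decides, because no other interval is named.

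**Conclusion.** The point holds as a conflict of confidence level, together with a margin that is not carried to the analysed scale. If the 95% interval in the Primary outcome section decides non-inferiority, power is about 83–84% by the normal approximation and about 79–80% with t on 18 df, not 90%. The loss is about 6 to 7 points on the Z basis. If a 90% two-sided interval decides, the stated power survives on either the difference or the retention-ratio scale by Z (about 88–89% with t).

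This assumes the plan's own inputs: 5% failure in both arms, ICC 0.004, and 10 equal clusters of 271 per arm. The ratio margin of 0.974 is derived here from 5% and 7.5%; the article does not state it.

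**What to change.** In the Primary outcome section, state one non-inferiority rule, on one scale, with the deciding interval named. Either of these would do:

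- the risk difference in non-retention, with its upper limit below 2.5 points (obtainable by standardisation from the log-linear model already planned); or
- the retention ratio, with its lower limit above 0.974, saying explicitly that retention is the modelled event.

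Then align the level in one of two ways. Use the 90% two-sided interval for the decision, which matches the one-sided 5% in the Sample size section. Or keep the 95% interval and restate power there as about 83–84% (about 79–80% with t on 18 df).

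The cost is a few sentences and, for the difference, one extra model output. Enrolment need not change. Keeping the 95% interval means accepting a less favourable stated power.

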Secondary study outcomes include virologic suppression, cost-effectiveness, and feasibility and acceptability to patients and to providers and will be measured at 12, 24, and 36 months. Viral load data will be obtained from medical records based on any available data recorded during the prior year. Cost-effectiveness will be analyzed from both patient and health system perspectives by surveying participants at enrollment about time and costs associated with each clinic visit and by creating inventories of all resources and costs to the facility and health system for each patient visit. Feasibility and acceptability will be measured by conducting qualitative in-depth interviews with a subset of 240 participants (120 per country) and 180 providers (90 per country) evenly balanced among the three study arms. A flowchart of the study is provided in Fig. 1. Our main hypothesis is that 6-month ART dispensing will be non-inferior to 3-month intervals for retention and virologic suppression, but that 6-month intervals will be cost-effective compared to 3-month intervals.

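### The main hypothesis compares 6-month with 3-month dispensing, but the sample size and primary analysis use standard of care as the reference, so no 6-month versus 3-month non-inferiority test is specified

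*Protocol article*

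**What the plan says.** The Methods/design section describes a "pragmatic, cluster-randomized, non-blinded, non-inferiority trial conducted at 30 health facilities in Malawi and Zambia" with three arms: standard of care, 3-month and 6-month dispensing. The places that name a reference arm do not agree.

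- **Background, last paragraph.** The main objective compares standard of care with 3-month and 6-month dispensing.
- **Intervention, last paragraph.** "Our main hypothesis is that 6-month ART dispensing will be non-inferior to 3-month intervals for retention and virologic suppression". Here the reference is the 3-month arm.
- **Sample size.** "about 5% of subjects would fail to be retained in care in the standard of care arm and 7.5% to be non-inferior", the 7.5% applying to the 3-month or 6-month arms. The reference is standard of care and the implied margin is 2.5 percentage points.
- **Data analysis, Primary outcome.** The endpoint is "retention in care at 12 months after study enrollment". A log-linear generalized estimating equation (GEE) will "estimate the risk ratios and associated 95% confidence interval for the effect of each intervention arm compared to standard of care". No 6-month versus 3-month contrast is named, and no margin for one.
- **Secondary outcomes.** Virologic suppression, also part of the main hypothesis, is analysed by the same methods and so against standard of care.
- **Data safety and monitoring plan.** "The study will be stopped early if we find a difference (at 12 or 24 months) between 3-month versus 6-month dispensing", at p<0.01. This returns to 3-month versus 6-month, but as a test for a difference.

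**The concern.** A non-inferiority claim needs a named reference, a margin and an error rate. For 6-month versus 3-month the article names the reference in the hypothesis and supplies neither of the other two. An analyst who follows the Primary outcome section reports two risk ratios against standard of care, and neither answers the main hypothesis.

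Two things are at stake. Non-inferiority of each intervention arm to standard of care does not carry over to the contrast between them, so a trial that succeeds on its planned analysis could be read as supporting a hypothesis that is false. And with two reference arms in the text, the contrast that carries the conclusion could be chosen after the data are seen. The Discussion says the result may inform dispensing guidelines.

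**Working it through.** **1. Inputs.** From Sample size: 30 clusters equally divided (10 per arm), 271 per cluster, 2710 per arm, ICC 0.004, power 90%, and "Using a one-sided *Z* test (unpooled) with a significance level of 0.05". Also from there: 5% failure under standard of care and a limit of 7.5%, so a margin of 0.025.

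**2. Reproducing the stated sample size.** Take true failure of 5% in both arms.
- n per arm without clustering = 2 × 0.05 × 0.95 × (1.645 + 1.282)² / 0.025² = 1301.7.
- With k = 10 clusters per arm, m = n(1 − ICC) / (k − n × ICC) = 1301.7 × 0.996 / (10 − 5.207) = 270.5, rounded up to 271.

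The stated 271 reproduces. It is the size for one intervention arm against standard of care.

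**3. What the same arms give for 6-month versus 3-month.** The arms are equal in size, so the formula carries over if the 3-month failure rate is known. The article gives 5% for standard of care only, so the rates below are assumptions.
- Design effect = 1 + 270 × 0.004 = 2.08.
- SE at 5% in both arms = √(2 × 0.05 × 0.95 × 2.08 / 2710) = 0.00854, and 0.025 / 0.00854 = 2.93.
- SE at 7.5% in both arms = √(2 × 0.075 × 0.925 × 2.08 / 2710) = 0.01032, and 0.025 / 0.01032 = 2.42.
- Power = Φ(margin/SE − z).

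| True failure, both arms (assumed) | One-sided 0.05 | One-sided 0.025 (two-sided 95% CI) |
|---|---|---|
| 5% | 90.0% | 83.3% |
| 7.5% | 78.2% | 67.8% |

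**4. Why the standard-of-care contrasts do not answer the hypothesis.** Assume true failure of 5% (standard of care), 2% (3-month) and 5% (6-month), one-sided 0.05 and the 2.5-point margin.
- 6-month versus standard of care: true difference 0, so the chance of passing is 90.0%, as in step 3.
- 3-month versus standard of care: SE = √((0.05 × 0.95 + 0.02 × 0.98) × 2.08 / 2710) = 0.00718. Φ((0.025 + 0.03)/0.00718 − 1.645) is practically 100%.
- 6-month versus 3-month: true difference +3 points, which is beyond the margin. A direct test would pass with probability Φ((0.025 − 0.03)/0.00718 − 1.645) = Φ(−2.34), about 1%.

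The planned analysis would succeed about nine times in ten here although the main hypothesis is false. A direct test would almost never make that error.

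**5. The margin and the model.** The margin comes from an absolute difference, while the GEE estimates risk ratios. The ratio equivalent of 7.5% versus 5% is 0.075/0.05 = 1.5 for failure, or 0.925/0.95 = 0.974 for retention. These agree only when the reference fails at 5%. If the reference fails at 2%, a failure ratio of 1.5 allows 3.0% (1 point worse). A retention ratio of 0.974 allows 1 − 0.98 × 0.9737 = 4.6% (about 2.6 points worse). The scale must therefore be stated.

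**The case against.** The strongest reply is that the article is mostly consistent: the objective, sample size and primary analysis all use standard of care, and the hypothesis sentence, supported by the stopping rule, is the one out of line. That stands. It means that 6-month versus 3-month cannot be presumed to govern, and restating the hypothesis is a legitimate repair.

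A second reply is that the comparison is not absent. The stopping rule compares 3-month with 6-month, and a three-arm log-linear model already contains that risk ratio as a contrast of its coefficients. Both are true. But a difference rule at p<0.01 cannot show non-inferiority, and a contrast that can be derived is not one that has been pre-specified with a margin.

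A third is that guidelines already recommend 3-month dispensing, so standard of care and the 3-month arm may behave alike. The Intervention section says that adherence to those guidelines varies and that intervals rest on provider opinion. Standard of care is a separate randomized arm. It is fair to add that the rates in step 4 of the working are illustrative, and the documents give no reason to expect that particular gap.

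Nor can the matter be left to an unseen analysis plan, because the Primary outcome section fixes the comparison explicitly.

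A reader might infer that the trial is too small for 6-month versus 3-month. The documents do not support that: the arms are equal, and the stated calculation gives the same 90.0% under the same assumptions.

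**Conclusion.** The point holds as a contradiction about the reference arm. Followed as written, the plan leaves the main hypothesis, for both retention and virologic suppression, without a specified non-inferiority test. This does not mean that the trial cannot estimate the 6-month versus 3-month effect, or that this contrast must come first. The model can produce it, and the investigators must say which reference governs.

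The consequence depends on how far the 3-month arm departs from standard of care. Under the assumed 5%, 2% and 5% rates, a false main hypothesis would accompany a pass for both intervention arms about 90% of the time. If the 3-month arm and standard of care fail at the same rate, the two references lead to much the same conclusion. The power figures rest on the stated ICC and the normal approximation, and on failure rates that the article gives for standard of care only.

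**What to change.** Choose one of two routes.

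**Route A: the 3-month arm is a reference for the main claim.** In Data analysis, Primary outcome, pre-specify 6-month versus 3-month retention at 12 months as a non-inferiority comparison from the same three-arm GEE, and state:
- the margin on the analysis scale, either as a ratio equivalent of 7.5% versus 5% (naming failure or retention) or as 2.5 points from a risk-difference model;
- an alpha that agrees with Sample size, since one-sided 0.05 there does not match a two-sided 95% interval;
- its place relative to the standard-of-care contrasts, fixed in advance by the investigators.

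In Sample size, add that 271 per cluster gives 90% power for this contrast only if both arms fail at 5% with one-sided 0.05, and give the other three figures from the table as the range. Say in Secondary outcomes whether the contrast also applies to virologic suppression.

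**Route B: standard of care is the intended reference.** Restate the main hypothesis in the Intervention section, and the conclusions drawn from it, against standard of care.

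Neither route needs more patients or data. Route A has a modest cost if the contrasts are tested in hierarchical order. If, for example, 6-month versus 3-month came first, then with 5% failure in all arms and one-sided 0.05 the chance of passing it and then 6-month versus standard of care is about 83%. The chance of passing all three contrasts is about 77%. At one-sided 0.025 these are about 73% and 63%. A fixed order spends no extra alpha, but it does lower the chance of passing whatever comes later, so the order should be a deliberate choice.

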### Blinding and allocation

Random assignment of matched clusters will be determined by computer. Clusters will be matched based on available information that could potentially predict outcomes, including ART cohort size and region. Matched clusters will then be randomly allocated with one receiving the 3-month intervention, one the 6-month intervention, and one the control condition. Allocation will be completed by the study analyst. Clusters will then be informed of the allocation. No attempt will be made to blind the sites or patients to their allocated group, as both providers and patients will be aware of the amount of medication dispensed and the timing between appointments.

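### The unstructured working correlation in the primary GEE cannot be estimated when the cluster is a facility of about 271 participants

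*Protocol article*

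**What the plan says.** In the Protocol article, Data analysis, Primary outcome, the primary analysis rests on retention 12 months after enrolment, so each participant contributes one binary result. The model is a log-link GEE giving risk ratios, with 95% intervals, for each intervention arm against standard of care. The GEE cluster is the facility, and the plan will "estimate robust standard errors using an unstructured correlation matrix".

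The Sample size section starts from a fixed number of facilities ("With 30 clusters available for randomization"), assumes "an equal number of clusters per arm, and an equal number of subjects per cluster", and describes clustering by one ICC of 0.004. It concludes that "we will need to enroll 271 subjects per cluster for a total of 2710 subjects per arm and 8130 total individuals". Under Blinding and allocation, facilities are matched in threes, "with one receiving the 3-month intervention, one the 6-month intervention, and one the control condition", which gives 10 facilities per arm.

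The Secondary outcomes section applies the same methods to virologic suppression. The article names no small-sample correction or reference distribution for the robust standard errors, and excludes none.

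**The concern.** An unstructured matrix suits a few ordered measurements in many independent units, such as three visits in thousands of people. Here the units are 30 facilities, and the measurements within each are some 271 interchangeable people. A separate correlation between the 5th and the 87th participant of a facility has no meaning, and it changes if the file is sorted differently.

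At stake is the primary result. If the fit fails, the model must be replaced. If software patches the matrix and prints an answer, that answer may be arbitrary and look far too precise. In a non-inferiority trial, intervals that are too narrow favour a false claim of non-inferiority.

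**Working it through.** **Inputs.** From the Sample size section: 30 clusters, 10 per arm, 271 participants per cluster, ICC 0.004, 5% failure with a limit of 7.5%, power 90%, and a one-sided unpooled Z test at 0.05. From Primary outcome: one binary result per participant, facility as cluster, log link, unstructured matrix.

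**1. The plan's own figure.** With both true rates at 5% and a margin of 7.5% − 5% = 2.5 points:

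- Individual-level n per arm = (1.645 + 1.282)² × 2 × 0.05 × 0.95 / 0.025² = 1301.7.
- With k = 10 clusters per arm, m = n(1 − ICC) / (k − n × ICC) = 1301.7 × 0.996 / (10 − 5.207) = 270.5, rounded up to 271.
- This gives 2710 per arm and 8130 in total. The design effect is 1 + 270 × 0.004 = 2.08.

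The stated sample size reproduces exactly. It uses one common correlation for every pair of participants in a facility.

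**2. Parameters against information.**

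- Unstructured: 271 × 270 / 2 = 36,585 correlations. Exchangeable: 1.
- Each of the 36,585 is an average over 30 facilities, with noise of about 1/√30 = 0.18 (0.19 in one simulated dataset) around a true value of 0.004.
- The moment estimate is a sum of 30 outer products, so its rank is at most 30 of 271. With the diagonal set to 1, one simulated dataset had 102 negative eigenvalues and another had 97. A correlation matrix can have none.

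**3. What software does with it.** One trial was simulated with 30 facilities of 271, 5% failure in every arm and ICC 0.004, and fitted with a standard log-link GEE routine:

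| Working correlation | Converged | Robust SE of the two log risk ratios | Fitted failure, reference arm |
|---|---|---|---|
| Exchangeable | yes | 0.144 and 0.114 | exp(−2.985) = 5.1% |
| Unstructured | no, stopped at 20 iterations; matrix had to be projected | 0.026 and 0.026 | exp(−2.629) = 7.2% |

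One dataset illustrates the problem and does not measure its average size. It does show that the routine can print a wrong estimate with a standard error four to six times too small (0.114 / 0.026 = 4.4; 0.144 / 0.026 = 5.5).

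**4. Conditional check: a plain sandwich with normal limits.** This assumes a workable working correlation and no correction specified elsewhere.

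- With 10 clusters per arm, the sandwich variance is about 9/10 of its target, so the SE ratio is √0.9 = 0.949.
- Relative to a corrected interval on t with 18 degrees of freedom, the width is 0.949 × 1.960 / 2.101 = 0.885.
- Simulated coverage of the nominal 95% risk-ratio interval (40,000 trials, ICC 0.004) is 91.7% when failure is modelled and 92.3% when retention is modelled. With a Kauermann-Carroll correction and t on 18 df it is 94.8% and 95.1%.
- On the risk-difference scale at the 7.5% v 5% limit (100,000 trials), one-sided error is 6.8% at nominal 5%. With the k/(k − 1) correction and t on 18 df it is 5.0%.
- At an assumed ICC of 0.02, plain coverage is 91.1% to 92.6%. An assumed coefficient of variation of 0.4 in cluster size does not change the picture.

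**The case against.** **Robust standard errors tolerate a wrong working correlation.** This is true in large samples when the working correlation is itself stably estimated. With 36,585 parameters and 30 clusters that condition fails, and step 3 shows the sandwich giving no protection.

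**Unstructured may refer to the visits.** The Background lists retention at 12, 24 and 36 months as primary outcomes, and three visits would need only three correlations. But the Primary outcome section fixes the primary analysis at 12 months and names the facility as the cluster, so this reading does not rescue the sentence.

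**The detail may sit in the full protocol or SAP.** For the working correlation this does not help: the structure is stated here, and another document would have to contradict it. For the small-sample correction the objection stands. A reader might infer that the plan uses uncorrected sandwich errors with normal critical values, but the article says only that the errors are robust. A condensed article commonly leaves the correction and degrees of freedom elsewhere, so step 4 is conditional.

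**The interim rule.** A reader might also infer that the p < 0.01 stopping rule is inflated. The Data safety and monitoring plan names no test or variance estimator, and its contrast is 3-month against 6-month dispensing, whereas the primary model compares each intervention with standard of care. The document does not support that claim, and none is made here.

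**Conclusion.** The primary model is wrong as written. An unstructured facility-level matrix for one outcome per participant asks for 36,585 order-dependent correlations from 30 clusters. It cannot be validly estimated, and it contradicts the single ICC in the sample size. This follows from the stated design alone and needs no assumption about omitted detail. Virologic suppression inherits the error. The stated sample size is unaffected.

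The small-sample issue is secondary and conditional. If no correction is specified elsewhere, coverage is about 92% instead of 95%, and one-sided error is about 7% at nominal 5%. These figures rest on 10 clusters per arm and beta-binomial clustering, and the error rate also on the margin as a risk difference.

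Nor does the problem force a change of model after the data are seen, since it can be corrected beforehand.

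**What to change.** In the primary outcome paragraph, replace the unstructured matrix with an exchangeable (or independence) working correlation at facility level, and apply the same to virologic suppression. Do this before any outcome data are analysed. Exchangeable matches the one-ICC assumption of the sample size. The change is one word and costs nothing in sample size or conduct.

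In the same sentence, unless another trial document already does so, name a bias-corrected sandwich (Kauermann-Carroll was checked above) and t limits on cluster-based degrees of freedom. Which df to use is for the SAP: 18 corresponds to 10 + 10 − 2 facilities in a two-arm contrast, and 27 to 30 − 3 in the three-arm model. With 27 df the simulated coverage was 94.2% (failure) and 94.6% (retention). The cost is a modestly wider interval: with 18 df, about 1 / 0.885 = 1.13 times the plain one.
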